### Interventions

#### Intervention

Participants randomised to the intervention arm will receive a prolonged, 5-day course of oral 500 mg amoxicillin, administered two times a day, to commence the day following the initial single-dose amoxicillin oral challenge.

#### Control

Participants randomised to the control arm will receive a prolonged, 5-day course of oral placebo (microcrystalline cellulose (MCC), prepared to be visually identical to the intervention, administered two times a day, to commence the day following the initial single-dose amoxicillin oral challenge).

#### Preparation and dispensing

A qualified pharmacy staff member will dispense the study medication in unique container numbers to a member of the investigator team. A second staff member will verify the dispensing. The participant or their caregiver should be instructed to maintain the product in the bottles provided throughout the course of dosing and return the bottles to the site at either a study visit or via a return registered post.

#### Study compliance

Participants will be asked to record the date and time of each dose of study medication using an electronic or paper diary. Compliance will be assessed at each scheduled visit by study staff who will ask the participant to count the number of capsules remaining. The following non-compliance cases will be recorded as protocol deviations:

Study medication missed for ≥2 consecutive doses.Study medication compliance<80%.

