#### PROSPECTOR-1

Compliance with the intervention (proportion of participants (n, %) taking at least 80% of the doses), need for unblinding (proportion of participants (n, %) being intentionally or unintentionally unblinded) and recruitment to eligibility ratio (proportion of participants (n, %) consented to the study from eligible participants). Subgroup analyses for admission setting (inpatient vs outpatient), risk (PEN-FAST score <3 vs ≥3) and severity (RegiSCAR score <2 vs ≥ 2) will be performed in the PROSPECTOR-1 study.

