### Participant timeline

The participant timeline is outlined in a schedule of enrolment, interventions and assessments for both studies (online supplemental table 2). After randomisation on day 0, participants will be provided with the study medication and a telehealth review will be scheduled for days 1, 5, 7 and 14 by a specialist allergy healthcare provider (ie, board-certified allergist, clinical immunologist and other clinicians with specialised training in allergy and immunology). If patients are inpatients at the time, then this review will be performed at the patient bedside. At each telehealth review, compliance will be recorded by reporting the number of doses taken, and participants will be asked about any other concurrent antibiotic therapy. If a positive oral challenge is reported, a summary of the patient-reported symptoms using a standardised questionnaire and clinical photography of any rash, cutaneous or mucosal changes will be sent to an independent review panel consisting of an allergist and dermatologist blinded to the intervention to ascertain if the reported reaction is an ‘immune-mediated adverse drug reaction’.

At days 30 and 90 post-randomisation, a telephone questionnaire and assessment of the medical record will be undertaken to assess for secondary outcomes including antibiotic-associated diarrhoea, *Clostridioides difficile* infection or acquisition of a multidrug-resistant organism. Patients at the day 90 follow-up will be unblinded if preferred by the site principal investigator, and those in the control arm will be offered a prolonged oral challenge.

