#### Progression from pilot to definitive trial

PROSPECTOR-2 will proceed immediately on completion of PROSPECTOR-1, provided the following criteria are met:

Compliance with study medication is ≥80%.Unblinding is ≤10%.Recruitment to eligibility ratio ≥80%.

If these criteria are not met, appropriate amendments to the study design of PROSPECTOR-2 will be made. If compliance is under 80%, additional reminders will be scheduled for participants. If unblinding exceeds 10%, the trial will be converted to open label. If the recruitment to eligibility ratio is lower than 80%, additional strategies for recruitment may be considered.

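### The PROSPECTOR-1 compliance outcome and its 80% progression criterion rest only on participant report, although the study bottles are returned to the site

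*Protocol article*

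**What the plan says.** Three sources of compliance data are described in the protocol article, and all come from the participant.

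- Diary (Study compliance): "Participants will be asked to record the date and time of each dose of study medication using an electronic or paper diary".
- Capsule count (Study compliance): "Compliance will be assessed at each scheduled visit by study staff who will ask the participant to count the number of capsules remaining".
- Stated doses (Participant timeline): "At each telehealth review, compliance will be recorded by reporting the number of doses taken". Reviews are on days 1, 5, 7 and 14, at the bedside for inpatients.

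Under Preparation and dispensing, participants are told to "return the bottles to the site at either a study visit or via a return registered post". No staff count of the returned contents is described.

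The outcome is defined under Outcomes, PROSPECTOR-1, as "Compliance with the intervention (proportion of participants (n, %) taking at least 80% of the doses". Under Progression from pilot to definitive trial the criterion reads "Compliance with study medication is ≥80" (per cent), with no arm named. The consequence of missing it is: "If compliance is under 80%, additional reminders will be scheduled for participants".

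**The concern.** A participant's own count, diary and recollection share one weakness: a person who missed doses can overstate intake in all three, and nothing in the described procedure would show it. Agreement among the three is therefore not independent confirmation.

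Here the measure decides something. The progression criterion is the only stated trigger for extra adherence support before the definitive trial. If over-reporting lifts the observed figure over 80%, that support is not added, and PROSPECTOR-2 starts with compliance lower than its investigators believe. A less biased source is already on its way to the site in the returned bottles, so accepting self-report as the only basis is an avoidable choice.

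**Working it through.** **Inputs from the protocol article**
- PROSPECTOR-1 sample size: 120, 60 per arm (Sample size).
- Stated precision: confidence interval narrower than 20 points for any proportion (Sample size), with exact 95% intervals (Statistical methods).
- Course: two doses a day for 5 days, so 2 × 5 = 10 doses. A compliant participant takes at least 0.80 × 10 = 8 (Interventions; Outcomes).
- Criterion: at least 80% of participants compliant. On all participants this needs 0.80 × 120 = 96.

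**Step 1. The plan's own figure.** The exact (Clopper-Pearson) 95% interval at n = 120 is widest at 60/120: 40.7% to 59.3%, or 18.5 points from unrounded limits. The stated precision reproduces. At the threshold, 96/120, the interval is 71.7% to 86.7%, 15.0 points wide.

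**Step 2. Effect of over-reporting on the criterion.** The article gives no compliance or misreporting data, so the rates here are assumptions. Let the true proportion compliant be 75%, and let self-report add d points. The number recorded as compliant is X ~ Binomial(120, 0.75 + d), and the criterion passes if X ≥ 96.

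| Over-reporting d | Recorded rate | Share of true non-compliers recorded as compliant, d / 0.25 | P(X ≥ 96) |
|---|---|---|---|
| 0 | 75% | 0% | 0.12 |
| 5 points | 80% | 20% | 0.55 |
| 10 points | 85% | 40% | 0.95 |

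**Step 3. Over-reporting needed at lower true compliance.** For the expected recorded rate to reach 80% from a true rate t, the share of non-compliers misrecorded must be (0.80 − t) / (1 − t):
- t = 75%: 0.05 / 0.25 = 20%
- t = 70%: 0.10 / 0.30 = 33%
- t = 60%: 0.20 / 0.40 = 50%

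Modest misreporting is enough when true compliance is just short of the threshold. A large shortfall needs a third to a half of non-compliers to be misrecorded.

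**Step 4. Should the threshold move to the amoxicillin arm alone?** That would need 0.80 × 60 = 48 of 60. The exact interval at 48/60 is 67.7% to 89.2%, 21.5 points wide, outside the stated aim. With accurate measurement and equal true compliance in both arms, the chance of a wrong pass rises:

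| True compliance, both arms | All 120 (≥ 96) | Amoxicillin arm only (≥ 48 of 60) |
|---|---|---|
| 75% | 0.12 | 0.23 |
| 70% | 0.01 | 0.06 |

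An arm-only threshold does better when compliance is clearly lower on amoxicillin than on placebo. With assumed rates of 70% on amoxicillin, the criterion on all 120 passes with the following probability, against 0.06 for the arm-only threshold:
- placebo 70%: 0.01
- placebo 75%: 0.04
- placebo 80%: 0.12
- placebo 90%: 0.55
- placebo 92%: 0.67

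**The case against.** The strongest reply is that this is an article, not the full protocol. Reconciling returned drug is routine, and a pharmacy manual not shown may require it. That would settle the matter if the article were silent, but it names the method, and the method is the participant's count. If a count of returned bottles exists elsewhere, the article should say that it, and not self-report, defines the outcome.

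It is also fair that the diary is dated and timed, that inpatients are seen at the bedside, and that a bottle count has its own errors: bottles not returned, and capsules discarded without being taken. These limit the gain from a count but do not remove it.

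A reader might infer more than the article supports:

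- *That the criterion pools the arms, so that good placebo compliance hides poor amoxicillin compliance.* No arm is named in the criterion, the outcome definition speaks of compliance with the intervention, and Statistical methods plans results by arm where feasible, so a low amoxicillin figure should be visible. A high chance of masking needs a gap of about 20 points between blinded arms taking visually identical capsules. No evidence for such a gap is given.
- *That amoxicillin exposure could be far below 80%.* The outcome is a proportion of participants reaching 8 of 10 doses, not mean exposure. A participant who took 7 doses is non-compliant but has had most of the course.
- *That PROSPECTOR-2 loses a stated amount of power because of this criterion.* Any such loss comes from non-compliance itself, and nothing shows that reminders would restore it.
- *That the per-protocol analysis inherits the same error.* The article does not define that population.

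A between-arm difference could also arise because participants stop after a reaction. The sample size section expects about 8% to have delayed reactions on prolonged challenge. If 85% would otherwise comply and all 8% stopped early (assumptions), apparent compliance would be 0.85 × 0.92 = 78%, and a threshold on that arm alone would fail 56% of the time. This is a good reason not to read a raw capsule count as poor delivery.

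**Conclusion.** The point stands as a measurement weakness in a primary PROSPECTOR-1 outcome and progression criterion. Every described source is self-report, while returned bottles offer a less biased one. The pass probabilities of 12%, 55% and 95% rest on an assumed true compliance of 75% and assumed over-reporting of 0, 5 and 10 points. They show sensitivity and are not a forecast. The consequence is modest: failing the criterion adds reminders and does not stop or redesign the trial, so a false pass costs only that corrective step. The documents do not support moving the threshold to one arm, which would lose the stated precision and, with equal compliance in both arms, raise the chance of a wrong pass.

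**What to change.** Under Study compliance, name the unblinded pharmacy's count of capsules in returned bottles as the primary compliance measure. Use the participant's count or diary only where no bottle comes back, and report how many participants were classified that way.

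Under Progression from pilot to definitive trial, state that the 80% threshold applies to all 120 participants, which keeps the stated precision. State also that the amoxicillin-arm figure, already planned, will be read beside it when deciding on extra reminders. Show participants who stopped because of a reaction separately, so that they are not mistaken for poor adherence.

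The cost is a little pharmacy work and no extra visit. Some bottles will not return, and a count cannot detect discarded capsules.

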### Outcomes

The primary outcomes for the PROSPECTOR studies are outlined below, with secondary outcomes listed in table 1.

**Table 1 T1:** Secondary outcome measures for **PRO**longed versus **S**ingle dose in **PE**nicillin oral **C**hallenge **T**esting double-blind parallel-group randomised placebo-c**O**ntrolled t**R**ial (PROSPECTOR) studies

	PROSPECTOR-1	PROSPECTOR-2
Positive oral challenge	Up to day 7 following the first hospital-administered single dose	Up to day 14 following the first hospital-administered single dose
Feasibility	Recruitment rate per site (recruitment/site/month) Randomisation to recruitment ratio (n, %) Withdrawal (n, %) Loss to follow-up (n, %) Missing data Protocol compliance (n, %)	Not applicable
Safety	Severe adverse reaction (n, %) Immune-mediated adverse event or severe adverse drug reaction (n, %) Non-immune-mediated adverse event (n, %) Any cutaneous adverse reaction (n, %)	Immediate severe adverse reaction (anaphylaxis or death) (n, %) Delayed adverse reaction (severe cutaneous adverse reaction) (n, %) Non-immune-mediated adverse event (n, %) Grade three or four adverse reactions as defined by World Allergy Organization (ref: Sanchez-Borges *et al*, 2019) (n, %) Any cutaneous adverse reactions (n, %)
Efficacy	*Clostridioides difficile* infection at days 30 and 90 (n, %) Isolation of a multidrug-resistant infection at days 30 and 90 (n, %)	*C. difficile* infection at days 30, 90 and 120 (n, %) Multidrug-resistant infection at days 30, 90 and 120 (n, %) Multidrug-resistant colonisation at days 30, 90 and 120 (n, %)
Cost-effectiveness	Cost-effectiveness of placebo vs open-label trial	Cost-effectiveness analysis of prolonged vs single-dose oral challenge
Quality of life	Not applicable	Health-related quality of life outcome, measured by shortened Drug Hypersensitivity Quality of Life Questionnaire (online supplemental table 3)^43^ at day 0 and day 90.

#### PROSPECTOR-1

Compliance with the intervention (proportion of participants (n, %) taking at least 80% of the doses), need for unblinding (proportion of participants (n, %) being intentionally or unintentionally unblinded) and recruitment to eligibility ratio (proportion of participants (n, %) consented to the study from eligible participants). Subgroup analyses for admission setting (inpatient vs outpatient), risk (PEN-FAST score <3 vs ≥3) and severity (RegiSCAR score <2 vs ≥ 2) will be performed in the PROSPECTOR-1 study.

#### PROSPECTOR-2

The proportion of positive oral challenges (ie, immune-mediated reaction up to and including day 7 following the first test dose, as adjudged by an independent blinded panel), n (%). Subgroup analyses for the following parameters: admission setting (inpatient vs outpatient), index reaction phenotype—delayed versus unknown timing, risk (PEN-FAST score 0 vs 1–2 vs ≥3), immunocompromised status, sex, region (Australia vs Europe vs Asia vs North America vs Africa), clinic type (specialised allergy clinic vs non-allergy clinic), index reaction severity (RegiSCAR <2 vs ≥2), index reaction phenotype—severe MPE (RegiSCAR score 1 or 2) versus RegiSCAR score <1 versus RegiSCAR score >2 and index reaction timing—delayed exanthema <5 years post index reaction versus delayed exanthema >5 years post index reaction.

### Participant timeline

The participant timeline is outlined in a schedule of enrolment, interventions and assessments for both studies (online supplemental table 2). After randomisation on day 0, participants will be provided with the study medication and a telehealth review will be scheduled for days 1, 5, 7 and 14 by a specialist allergy healthcare provider (ie, board-certified allergist, clinical immunologist and other clinicians with specialised training in allergy and immunology). If patients are inpatients at the time, then this review will be performed at the patient bedside. At each telehealth review, compliance will be recorded by reporting the number of doses taken, and participants will be asked about any other concurrent antibiotic therapy. If a positive oral challenge is reported, a summary of the patient-reported symptoms using a standardised questionnaire and clinical photography of any rash, cutaneous or mucosal changes will be sent to an independent review panel consisting of an allergist and dermatologist blinded to the intervention to ascertain if the reported reaction is an ‘immune-mediated adverse drug reaction’.

At days 30 and 90 post-randomisation, a telephone questionnaire and assessment of the medical record will be undertaken to assess for secondary outcomes including antibiotic-associated diarrhoea, *Clostridioides difficile* infection or acquisition of a multidrug-resistant organism. Patients at the day 90 follow-up will be unblinded if preferred by the site principal investigator, and those in the control arm will be offered a prolonged oral challenge.

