#### Blinding

Participants (and their caregivers if applicable) as well as study investigators and research staff will be blinded to the assigned intervention. Adverse Event Review Panel members will be blinded to the assigned intervention. Clinical trials pharmacists will be unblinded.

Participants may be unblinded during the 7-day follow-up period in the event of a serious adverse event (SAE) or grades 3 or 4 adverse event and if the site principal investigator deems this appropriate. If a participant’s assignment is revealed, the Sponsor and Coordinating Principal Investigator will be notified within 24 hours of unblinding. The date and reason for the blind broken must be recorded in the source documentation and case report form. All participants may be unblinded at the 90-day follow-up to allow for those in the control arm to receive a prolonged challenge if that is the site’s practice or preference.

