### Harms

Adverse events will be recorded from the time of randomisation until day 90. Patients will be supplied with a prescription for oral corticosteroids and second-generation antihistamines on hospital discharge, only to be used in the event of an immune-mediated positive oral challenge, as instructed by the site investigators at the time of the days 1, 5, 7 and 14 reviews. Participants will be instructed by site investigators to fill this script at their own expense if required.

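### PROSPECTOR-2 lists three infection outcomes at day 120, but from day 90 controls may be unblinded and offered the prolonged challenge, so the day-120 contrast no longer compares prolonged with single-dose challenge

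*Protocol article*

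**What the plan says.** All references are to the protocol article.

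- **Outcomes, Table 1, PROSPECTOR-2 efficacy row.** Three outcomes carry a day-120 reading. The two infection outcomes appear as "infection at days 30, 90 and 120 (n, %) Multidrug-resistant infection at days 30, 90 and 120 (n", where the first entry is C. difficile. The third is "Multidrug-resistant colonisation at days 30, 90 and 120 (n".
- **Outcomes, Table 1, PROSPECTOR-1 column.** The corresponding entry stops earlier: "Isolation of a multidrug-resistant infection at days 30 and 90 (n".
- **Participant timeline.** At day 90, patients may be unblinded if the site principal investigator prefers, and "those in the control arm will be offered a prolonged oral challenge". The same section describes the late contacts: "At days 30 and 90 post-randomisation, a telephone questionnaire and assessment of the medical record will be undertaken". The full schedule is in online supplemental table 2, which is not shown.
- **Blinding.** The option is repeated: "All participants may be unblinded at the 90-day follow-up to allow for those in the control arm to receive a prolonged challenge", where this is the site's practice or preference.
- **Harms.** "Adverse events will be recorded from the time of randomisation until day 90".
- **Intervention.** The randomised exposure is five days of oral amoxicillin starting the day after the initial challenge. The abstract describes a prolonged challenge as five days.

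**The concern.** The control arm is there to show what happens after a single dose alone. Once controls can take the prolonged course, the arms stop differing in the way randomisation made them differ. At day 120 an intervention participant is about 115 days past the course, while a control who accepted the offer started it at most 30 days earlier.

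C. difficile infection and multidrug-resistant infection or colonisation are possible harms of antibiotic exposure. If the longer course raises their risk, dilution at day 120 makes it look less harmful than it is. A measure confined to the period after day 90 could make the control arm look worse. Participants may also know their allocation by then. The article states no handling of data after the crossover, and does not say whether an outcome at day 120 is cumulative from day 0, counted since the previous reading, or the status on that day.

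**Working it through.** **1. How many controls could cross over.** The only relevant stated figure is the sample size. With 3% against 8%, two-sided 5% significance, 85% power and pooled variance (mean proportion 0.055):

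n = [1.960·√(2·0.055·0.945) + 1.036·√(0.03·0.97 + 0.08·0.92)]² / 0.05² ≈ 372 per arm.

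This reproduces the plan's 372. Allowing 10% loss, 372/0.9 rounds up to 414 per arm, or 828 in total, against the stated 830 (415 per arm). The controls in follow-up at day 90 therefore number roughly 372 (after the planned loss) to 415 (no loss). Uptake is not given; three assumed values:

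| Uptake | Of 372 | Of 415 |
|---|---|---|
| 25% | 93 | 104 |
| 50% | 186 | 208 |
| 100% | 372 | 415 |

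**2. Time since the course at day 120.** Intervention: 120 − 5 = 115 days since the last day of dosing. Crossed-over control: at most 120 − 90 = 30 days since starting.

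**3. Effect on the risk difference (RD).** Every risk input here is an assumption. Let e be the excess risk from one 5-day course, set to 1 percentage point. Let f, g and h be the shares of e that arise 0-30, 31-90 and 91-120 days after the course, summing to 1. Let c be the share of controls who take the course on day 90. Baseline risk is equal in both arms and cancels.

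- Cumulative RD at day 120 = e(f + g + h) − c·e·f
- RD over days 91-120 = e·h − c·e·f
- RD at day 90 = e(f + g), with no contribution from c

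For example, with f = 0.70, g = 0.25, h = 0.05 and c = 0.5, the cumulative RD is 1.00 − 0.5·0.70 = +0.65 and the days 91-120 RD is 0.05 − 0.35 = −0.30.

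| (f, g, h) | Measure | c = 0 | c = 25% | c = 50% | c = 100% |
|---|---|---|---|---|---|
| (0.70, 0.25, 0.05) | Cumulative | +1.00 | +0.825 | +0.65 | +0.30 |
| (0.90, 0.10, 0) | Cumulative | +1.00 | +0.775 | +0.55 | +0.10 |
| (0.50, 0.40, 0.10) | Cumulative | +1.00 | +0.875 | +0.75 | +0.50 |
| (0.70, 0.25, 0.05) | Days 91-120 | +0.05 | −0.125 | −0.30 | −0.65 |
| (0.90, 0.10, 0) | Days 91-120 | 0.00 | −0.225 | −0.45 | −0.90 |
| (0.50, 0.40, 0.10) | Days 91-120 | +0.10 | −0.025 | −0.15 | −0.40 |

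Values are percentage points. The cumulative difference shrinks by the fraction c·f: 25% to 45% at half uptake and 50% to 90% at full uptake. It does not change sign. The days 91-120 difference turns negative once c exceeds h/f, which is about 7% (0.05/0.70), 0% (0/0.90) and 20% (0.10/0.50) for the three patterns. A current-status measure, the natural reading for colonisation, is open to the same reversal, although its size would also depend on how long colonisation lasts.

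**4. The day-90 reading.** The RD at day 90 is +0.95, +1.00 and +0.90 for the three patterns, whatever the later uptake.

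**The case against.** The strongest reply is about reach. Only the last of three time points for three secondary outcomes is touched. The primary outcome is read at day 7 and the secondary positive-challenge outcome at day 14. The infection outcomes also have day-30 and day-90 readings, and the sample size does not rest on day 120. All of this stands and limits the severity.

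A second reply is that comparing arms as randomised still estimates the effect of an assigned strategy that includes a later optional challenge, and that handling of crossover belongs in the promised statistical analysis plan. The first half is true. But the stated PROSPECTOR-2 objective is prolonged against single-dose challenge, and the strategy effect would vary with site preference and uptake. On the second half, the protocol itself fixes both the day-120 outcome and the day-90 offer. An analysis plan can define how to treat the later data, but it cannot by itself keep controls unexposed.

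Third, uptake and timing are unknown, and a challenge taken after day 120 contaminates nothing. That stands, and it is why the sizes above are scenarios.

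Two stronger inferences are tempting. A reader might conclude that day 120 has no assessment point, because the text describes late contacts at days 30 and 90 only. The schedule is in a supplemental table that is not shown, so this cannot be established. A reader might also conclude that reactions to the later challenges will go unrecorded. The Blinding section ties the offer to site practice, so it may be care outside the trial's recording. The text shows only that the two provisions meet at day 90 without being reconciled.

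**Conclusion.** The point holds for the day-120 readings of C. difficile infection, multidrug-resistant infection and multidrug-resistant colonisation in PROSPECTOR-2. Followed as written, the plan permits controls to take the randomised exposure up to 30 days before those readings.

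If the course acts in one direction, a cumulative count is biased toward no difference in proportion to uptake. A reader might infer that the result will reverse sign. That requires a current-status or days 91-120 count, and the article does not say which count is meant. The size rests on assumed uptake, on crossover taking place on day 90, and on assumed risk inputs; none of these is in the documents.

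Nor does the point threaten the trial's main conclusion, since the earlier outcomes precede the crossover. PROSPECTOR-1, whose infection outcomes end at day 90, is not affected. This is a moderate defect in secondary outcomes with a simple remedy.

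**What to change.** In Table 1, make day 90 the last randomised comparison for the three outcomes. Then either drop day 120 as a between-arm outcome, or keep it as a descriptive report split by whether a prolonged challenge was taken after day 90. Carry the same wording into the analysis plan.

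Reconcile the Harms section, where adverse-event recording ends at day 90, with the Participant timeline and Blinding sections, which offer a further challenge from that day.

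The cost is a change of wording. No participants are added, and the offer to controls need not change. What is lost is a late between-arm comparison that is already contaminated. Under the three patterns assumed above, even without crossover it would add at most 0.10 percentage point to the day-90 difference (1.00 − 0.90).
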